## Abstract

**Background:**

Leisure participation is essential for children’s health and well-being and is also a fundamental human right; however, children and youth with disabilities face significant barriers to participation compared with their peers without disabilities. The Jooay App was developed to address gaps in information and access to adaptive and inclusive leisure activities. A new gamification-based version of the Jooay App was co-designed with users, including youth with disabilities, parents, and health care professionals.

**Objective:**

This study aims to describe a study protocol to implement and evaluate the gamified version of the Jooay App using a patient-oriented approach to increase awareness about adaptive and inclusive leisure activities and promote participation in leisure among children and youth with disabilities.

**Methods:**

A hybrid type II effectiveness-implementation study will be conducted. The Consolidated Framework for Implementation Research (CFIR) will guide implementation strategies, including the expansion of knowledge broker (KB) networks to raise the profile of adaptive and inclusive leisure activities in Canada. An interrupted time series (ITS) design will be used to evaluate implementation outcomes across 5 provinces in Canada. Process evaluation will analyze inner and outer setting characteristics, KB strategies, and community resource mobilization. Effectiveness outcomes will be assessed through two phases: (1) a nonrandomized mixed methods pilot feasibility study of the app, where acceptability, engagement, implementation, and potential benefits will be measured, and (2) an ITS at the population level, where overall app usage (eg, clicks, logins, and time spent), individual gamification feature metrics, and user feedback will assess effectiveness outcomes.

**Results:**

The project was funded by the CHILD-BRIGHT (Child Health Initiatives Limiting Disability–Brain Research Improving Growth and Health Trajectories) Network through the Strategy for Patient-Oriented Research, Canadian Institutes of Health Research, in September 2025, and data collection is expected to occur from March 2026 to June 2027. As of manuscript submission, 12 KBs have been recruited, the ITS study and data analysis have not yet begun, and the study results for the implementation and effectiveness components are expected to be published in fall 2027. Findings will be disseminated via peer-reviewed publications, conference presentations, educational materials, social media, community events, and reports. Outputs will include a summary of findings in lay language, in both French and English, including short videos, infographics, and posters for various social media platforms. Community organizations will assist in further dissemination through their networks.

**Conclusions:**

This study will evaluate both the effectiveness and the implementation of the gamified Jooay mobile app to promote participation in leisure among children and youth with disabilities using a hybrid effectiveness–implementation design. By applying the CFIR framework, this study aims to generate evidence about how the Jooay App can be effectively implemented across Canada and expand scholarship on the implementation of technology for equity-deserving groups.

## Introduction

### Background and Rationale

Participation is an essential component of childhood development and is a human right for children and youth [1,2]. However, children and youth with disabilities experience limitations in participation in leisure activities compared to those without disabilities [3]. Their limited participation can be attributed to various barriers, including physical (eg, accessibility and built environment), social (eg, peer support), attitudinal (eg, perceptions of disability), and institutional factors (eg, policies and the availability of adapted programs) [4]. Additionally, a critical barrier that requires attention is the lack of accessible information regarding adaptive and inclusive leisure activities, which further hinders participation [5].

Developed in 2015, the Jooay App is a mobile health (mHealth) solution designed to address this community need. Since its launch, its user base has steadily grown, with reported benefits including integration into rehabilitation and education interventions, physician-endorsed health promotion, increased awareness among parents and youth, and greater visibility for community leisure programs [6].

Preliminary studies indicate that information on adaptive and inclusive leisure programs is unevenly distributed across Canada, with lower availability in provinces experiencing greater social and material deprivation and outside urban centers [7]. Provincial dialogs with interest holders and local knowledge broker (KB) networks have been identified as effective in raising awareness and expanding knowledge of these activities [8]. Additionally, various strategies, such as in-app surveys and tailored responses during the COVID-19 pandemic, have been tested to enhance user engagement [9]. Our latest study suggests that incorporating targeted engagement strategies within the app, in addition to a targeted implementation strategy with various KBs, could further promote participation in leisure activities [6].

Gamification, which is integrating game-like features into mobile apps, can enhance user engagement and can promote health behavior change in various populations [10]. The use of mHealth and gamification in health care is expanding, with studies exploring its potential for encouraging healthy behaviors in children with disabilities. However, such technologies often lack user-centered design [11]. To address this gap, we co-designed a gamified version of the Jooay App following human-centered co-design principles, incorporating insights from youth with disabilities, parents, clinicians, and community organizations through interviews, co-design sessions, and usability studies [12].

mHealth interventions can enhance access to evidence-based services. However, achieving successful implementation and ensuring their long-term sustainability in real-world contexts remain complex challenges. Factors such as poor integration within existing systems, limited involvement of key interested parties, and the lack of sustained support mechanisms often result in low uptake and inconsistent use, even when the intervention itself is well-designed [13]. Increasingly, it is recognized that effective implementation requires tailored, theory-driven, and contextually responsive strategies that address barriers at the organizational, provider, and patient levels, rather than relying solely on passive dissemination or technological innovation [14].

Community-based interventions, particularly those involving mHealth tools like the gamified Jooay App and KB networks, face distinct implementation and sustainability challenges stemming from their reliance on multilevel coordination across sectors (eg, health, education, recreation, and municipal services), voluntary engagement, and context-specific adaptation [15]. Unlike initiatives embedded within a single organization, these interventions depend on partnerships with diverse interest holders operating under varying mandates, resources, and priorities, leading to variability in local infrastructure, leadership support, and organizational readiness that can affect uptake, fidelity, and equitable reach across settings—especially in rural or socioeconomically disadvantaged provinces of Canada, where information access remains uneven [16]. Key barriers include logistical difficulties in recruiting and retaining diverse KBs from backgrounds such as health care providers, educators, families, and youth with disabilities, which may compromise representation and contextual relevance [17]. Sustained engagement of community partners is often constrained by limited funding, staff turnover, competing priorities, resource inequities, and inadequate ongoing support mechanisms post initial implementation [15]. Broader sustainability issues for such multisystem efforts encompass challenges in aligning the app and KB strategies with existing health care, educational, and community systems without continuous external resources, often resulting in uneven dissemination, inconsistent mobilization of local networks, reduced uptake, and eventual fade-out, even with strong initial design and theory-driven frameworks like the Consolidated Framework for Implementation Research (CFIR).

KB networks are known as effective ways to implement public health interventions [8], especially for complex interventions that are not localized or delivered directly by a health care provider and require multiple systems and communities to interact for their collective benefit [18]. The KB is an individual who represents an interest group or an organization representative who “synthesizes local community and patient data with general and specific research knowledge to assist users in translating the evidence into locally relevant recommendations for policy and practice” [19]. The KB’s knowledge of the local context (eg, provincial resources and policies supporting leisure, or local school board or municipality leisure incentives) can help leverage the community resources and ensure the best dissemination strategies are used.

### Objectives

The primary objective of this study is to evaluate whether the deployment of the gamified version of the Jooay App is associated with changes in app engagement compared with the previous nongamified version. Specifically, we will examine changes in app engagement following the deployment of the gamified Jooay App, using an interrupted time series (ITS) analysis of aggregated app analytics data.

The secondary effectiveness and feasibility objectives are to examine changes in specific engagement indicators, including app sessions, active users, duration of use, frequency of use, and use of key app features; to evaluate the feasibility of the gamified Jooay App among youth with disabilities, parents, and clinicians; and to explore postdeployment participation-related outcomes, including planned activities, attended activities, satisfaction, and perceived achievement.

The implementation objectives are to assess the process of implementing and scaling up the gamified Jooay App across participating Canadian provinces; to describe the expansion, role, and activities of the Jooay KB networks across these provinces; to identify provincial barriers and facilitators influencing app uptake, implementation, and sustainability; and to examine how the app and KB networks support the identification of community-based play and leisure opportunities for children and youth with disabilities.

## Methods

### Study Design

We will adopt a hybrid type II effectiveness-implementation design, testing the implementation strategy while observing and gathering information on the intervention’s impact on relevant outcomes [20,21].

### Theoretical Framework

In this study, we will use the CFIR to implement and evaluate the scale-up and expansion of the app use through the expansion of KB networks [22]. KB networks will mobilize information about the app and foster engagement with the app and community activities. We will use the health behavior framework to guide the individual intervention evaluation for the user-designed gamification features to increase individual engagement with the app [23].

### Sampling

#### Preimplementation

The preimplementation phase involves a human-centered co-design process to identify and integrate evidence-based gamification features into the Jooay App. Additionally, we will codevelop informational materials to guide KBs and users in maximizing app engagement. KBs will receive training on the gamified app, along with codeveloped dissemination materials (eg, videos and infographics). Training will emphasize active engagement, including writing reviews, adding activities, notifying organizations of their inclusion in the Jooay database, participating in the “Community Connecting to Play” shared KB journals, and engaging with Jooay social media.

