#### Implementation

The KB strategy will be implemented and evaluated using an ITS. This approach is well-suited for assessing the effectiveness of population-level health interventions and testing their impact on specific outcomes within a defined impact model. We will conduct a multisite ITS study, accounting for the KB interventions in 5 different provinces. KBs who participated in previous Jooay studies will be invited to participate in a focus group to (1) review past KB practices, (2) rank strategies based on perceived effectiveness, (3) identify contextual factors influencing implementation, and (4) refine strategies for different settings. New KBs will be recruited and trained through interactive online workshops in purposefully selected provinces (British Columbia, Alberta, Saskatchewan, Ontario, Québec, and Yukon) and across sectors (families, youth, health, and education). KBs will identify new activities, update program information in their provinces, identify populations who may not know about the app, and develop strategies to disseminate within these provinces and promote the app to users (youth, families, clinicians, and educators) and community organizations within their scope of reach. Their insights will inform a 2-fold approach to innovation, sustainability, and use: (1) an automated system to optimize resource identification and updates within the Jooay database, and (2) an organic, human, and community-led dissemination process.

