#### Effectiveness

We will evaluate the effectiveness of the app use on users’ engagement and participation in the community through two phases: (1) a nonrandomized mixed methods pilot feasibility study at the individual level and (2) an ITS study of the Jooay App implementation at the community level. Participants will include clinicians, parents of youth with disabilities of all ages, youth with disabilities aged 14 years and older, and educators. They will be recruited from the current user-base of the Jooay App (over 6000 users across Canada), through rehabilitation centers, community organizations, and schools that are part of the Jooay App research group, and social media and partner organizations’ mailing lists.

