### Procedures

#### Implementation

KBs will be recruited across multiple Canadian provinces (British Columbia, Alberta, Saskatchewan, Ontario, Québec, and Yukon) and sectors (health, education, community organizations, families, and youth networks). Recruitment will follow a purposive and network-based strategy. Existing KBs and community partners involved in previous Jooay initiatives will first be invited to participate in an online focus group to review prior brokering strategies and identify contextually relevant approaches for scale-up. Additional KBs will be identified through professional networks, stakeholder recommendations, and community organizations (“natural” KB networks), including clinicians, educators, rehabilitation program managers, community leaders, and information hubs. Interested individuals will receive an email invitation outlining study objectives, procedures, and time commitment. Electronic informed consent will be obtained prior to participation. KBs will receive CAD $100 (CAD $1=US $0.72 as of March 1, 2026) per month for 6 months in recognition of their participation.

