Prior to implementation, KBs will complete an online readiness-to-implement questionnaire informed by the capability, opportunity, motivation–behavior (COM-B) model [25]. The questionnaire will assess capability (knowledge of Jooay and inclusive leisure resources), opportunity (access to relevant professional and community networks), and motivation (intention and perceived importance of dissemination) [25]. Results will inform tailoring of training and support strategies. KBs will participate in monthly online meetings (Microsoft Teams) over 6 months. Meetings will include structured check-ins on dissemination activities, discussion of barriers and facilitators, and peer exchange of strategies across provinces. At the first meeting, KBs will determine preferred communication channels for ongoing exchange (eg, WhatsApp; Meta Platforms, Inc, or other group platforms). Meeting minutes and field notes will be documented for process evaluation. In the second meeting, we will provide a workshop on the new gamified version of the Jooay App. The latter meetings will be structured around the COM-B model based on the readiness to disseminate survey results. One meeting will focus on capability (knowledge of Jooay and inclusive leisure resources), another on opportunity (access to relevant professional and community networks), and one on motivation (intention and perceived importance of dissemination). KBs will be responsible for 3 main aspects. The first is identifying adaptive and inclusive leisure activities in their province. The second is sharing updated program information with the Jooay team. The third is disseminating the Jooay App to youth, families, clinicians, educators, and community organizations through existing networks. KBs will document dissemination activities using an online activity log. At the end of the 6-month implementation period, semistructured individual interviews will be conducted with KBs via Microsoft Teams. Interviews will explore dissemination experiences, perceived effectiveness of implementation strategies, contextual barriers and facilitators, and sustainability considerations. Interviews will be audio-recorded, transcribed verbatim, and anonymized. Process data will include monthly meeting notes, KB activity logs, and workshop evaluations. Qualitative data will be analyzed using thematic analysis. Deductive coding will be guided by the CFIR, with attention to intervention characteristics, inner setting, outer setting, characteristics of individuals, and implementation processes. The 2 researchers will independently code transcripts and resolve discrepancies through discussion. Descriptive statistics will summarize readiness-to-implement scores and dissemination indicators.

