### Variables and Outcomes

#### Implementation

The implementation outcomes of this study include both process and intervention-related measures. The implementation process will be analyzed using the CFIR, focusing on outer setting, inner setting, and individual characteristics. The outer setting includes external influences such as patient needs, resources, and organizational networks. KBs recruited from each setting will undergo an initial assessment to identify key considerations, constraints to sustaining the KB role beyond the study, and an intake analysis of individual actions. These factors will be examined in initial KB analyses, monthly KB meetings, and a post hoc multisite analysis. Additionally, external factors such as cosmopolitanism (organizational networking), peer pressure, and policies or incentives supporting leisure-related outcomes will be assessed to determine their role in technology adoption and resource integration. The inner setting includes organizational characteristics affecting implementation, including team culture, intervention compatibility, goal-setting structures, leadership engagement, and implementation climate, which will be analyzed qualitatively through meeting minutes from monthly KB sessions. Individual characteristics, including KBs’ beliefs, knowledge, self-efficacy, and personal attributes influencing implementation, will be assessed during onboarding interviews with the research coordinator. User characteristics (eg, disability type, age, socioeconomic status, language, and technology familiarity) will be analyzed preimplementation during user-centered design activities and pilot testing. These insights will inform KBs’ strategies and interventions.

The implementation and intervention outcomes will assess the expansion of KB networks using social network analysis, as well as the growth in Jooay App users and their engagement levels. Additionally, partners with lived and living experiences (PWLEs) identified increased community awareness of leisure activities as a key implementation outcome, emphasizing its significance in post-COVID public policy and service restructuring. This outcome will be measured through quantitative indicators, including social network analysis and the number of new organizations and activities added to the app during the intervention period, compared with previous registration cycles.

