### Community Level

The effectiveness of the gamification-based mobile app intervention will be assessed primarily through user engagement metrics collected through app analytics, including the number of clicks, logins, active time spent, access frequency of individual gamification features, comments, and reviews. These data will provide insights into how youth, caregivers, and professionals interact with the app over time. Additionally, differential outcomes will be examined for health care and education professionals, focusing on the integration of community participation into intervention plans and health promotion strategies. For youth, the impact of the intervention will be evaluated based on increased participation in community activities, collected from the “Activity Planner” and “My Summary” features within the Jooay App.

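### New listings are read as community awareness, and reviews as effectiveness, although knowledge brokers are trained or assigned to produce both and their content is not separated

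*Protocol article*

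**What the plan says.** **What KBs do.** Sampling – Preimplementation describes their preparation: "Training will emphasize active engagement, including writing reviews, adding activities", followed by telling organizations that they are listed. Sampling – Implementation assigns the work: "KBs will identify new activities, update program information in their provinces, identify populations who may not know about the app". Procedures – Implementation gives three responsibilities. "The first is identifying adaptive and inclusive leisure activities in their province" is how the list opens; passing updated program information to the Jooay team is the second, and spreading the app is the third. KBs keep an online log of their dissemination activities. They receive CAD $100 "per month for 6 months in recognition of their participation". The Results section reports 12 already recruited.

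**What is counted.** Variables and Outcomes – Implementation names greater community awareness of leisure activities as a key implementation outcome. Its quantitative indicators are social network analysis and "the number of new organizations and activities added to the app during the intervention period, compared with previous registration cycles". Variables and Outcomes – Community Level assesses effectiveness primarily through engagement metrics, "including the number of clicks, logins, active time spent, access frequency of individual gamification features, comments, and reviews".

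**Whose activity is counted.** Sample Size aggregates engagement monthly over all users who are eligible, without defining eligibility. No section sets KB-authored content apart, and none says that it is included.

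**The concern.** An outcome meant to show a change in the community should not be one that the delivery team produces as part of its job. Two stated outcomes have this weakness.

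The first is the listings count. KBs are trained to add activities and assigned to find them. A higher count shows that KBs did their work. It does not show that families, youth or organizations became more aware of what is available. The construct and its indicator are both fixed in the article, so a more detailed analysis plan would not remove the difficulty.

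The second is reviews. They are listed as an effectiveness metric, and writing them is a training emphasis for the people who deliver the implementation strategy.

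If nothing changes, both counts could rise while no user outside the KB network behaves differently, and the report would present delivery as community impact.

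**Working it through.** **Step 1: match KB behaviours to counted outcomes.**

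| KB behaviour | Where stated | Outcome that counts it | Read as |
|---|---|---|---|
| Adding or identifying activities, sharing program information with the team | Sampling – Preimplementation; Sampling – Implementation; Procedures – Implementation | New organizations and activities added | Community awareness |
| Writing reviews | Sampling – Preimplementation (training only) | Reviews | Effectiveness |
| Using the app | Implied by training and workshop | Clicks, logins, active time | Effectiveness |

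The first two rows overlap directly. The third depends on how large a share of users the KBs are.

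**Step 2: number of KBs.** Sample Size asks for at least 1 in each of 6 jurisdictions, 6 × 1 = 6, which reproduces the stated minimum. Two in each gives 6 × 2 = 12, which matches the 12 recruited.

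**Step 3: reviews or listings.** The article gives no baseline rate and no output per KB, so both are assumptions here.

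Apparent rise = (12 × items per KB per month) / baseline items per month.

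| Assumed baseline per month | 1 per KB (adds 12) | 2 per KB (adds 24) | 5 per KB (adds 60) |
|---|---|---|---|
| 5 | 240% | 480% | 1200% |
| 20 | 60% | 120% | 300% |
| 50 | 24% | 48% | 120% |
| 100 | 12% | 24% | 60% |
| 500 | 2.4% | 4.8% | 12% |

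These are rises during active KB months. If all 6 KB months fall within 12 post-deployment months, the average over those 12 is half as large. At a baseline of 50 and 2 per KB, for example, 48% × 6/12 = 24%.

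**Step 4: general engagement.** Sampling – Effectiveness puts the user base above 6000. KB share = 12/6000 = 0.2% (6/6000 = 0.1% at the minimum).

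Inflation of the total = 12 × (KB intensity relative to an average user) / active users. The number of active users and the relative intensity are assumptions.

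- 6000 active, equal intensity: 12/6000 = 0.2%
- 6000 active, 20 times the intensity: 240/6000 = 4%
- 300 active, equal intensity: 12/300 = 4%
- 300 active, 5 times the intensity: 60/300 = 20%

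The direct effect on clicks, logins and time is small unless few registered users are active and KBs use the app much more than others do.

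**The case against.** The strongest reply is that this is a hybrid design whose purpose includes testing the implementation strategy, so KB output is a proper thing to count. The listings are declared an implementation outcome and sit beside social network analysis. That stands as a defence of counting them. It does not defend calling the count community awareness.

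Account eligibility rules may also sit in a fuller document. That is fair for reviews: inclusion of KB content is inferred from the undefined eligible population and the absence of any separation. It does not help the awareness indicator, whose meaning is fixed in the article.

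Earlier KB strategies were used in these provinces (Setting – Implementation), so past registration cycles may already contain KB-sourced listings. This could narrow the contrast, but it does not turn the count into a measure of awareness.

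A reader might infer four stronger things that the article does not support:

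- **KBs are paid to write reviews.** The payment is a flat monthly sum for taking part, and reviews are not among the three responsibilities.
- **The primary interrupted time series is compromised.** The Objectives name sessions, active users, duration, frequency and feature use, not reviews, and KBs are about 0.2% of the user base.
- **Pilot participants tilt the baseline.** They use a test version, the pre-deployment segment is defined as data from the nongamified version, and the pilot is analysed separately. Carry-over of onboarded and reminded pilot users into the post-deployment months is possible and not addressed, but that is a lesser matter.
- **Unequal cycle length distorts the comparison.** The article gives neither the cycle length nor whether raw counts are compared, so a rate is a precaution rather than the correction of a shown error.

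**Conclusion.** The point holds for two outcomes. The listings count cannot be interpreted as community awareness, because KBs are assigned to find what it counts. This follows from the text without any numerical assumption. Reviews have the same weakness as an effectiveness metric if KB-authored reviews are in the data, which the article neither states nor rules out.

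The size is unknown. Over the assumed ranges, 12 KBs could account for an apparent rise anywhere from 2.4% to 1200%, from negligible to dominant. No narrower figure can be justified from the document, and this is a reason to set the rule before the data are seen. Clicks, logins and active time are probably little affected, on the assumption that a good part of the more than 6000 users is active. The primary engagement analysis is not put in doubt on this ground. The change should be made, but the design does not depend on it.

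**What to change.** 1. Tag every new listing and review by source: KB, study team acting on KB information, organization, or other user. The submitting account alone is not enough, because KBs pass program information to the team. The KB activity logs can support the tagging. It must be done before the analytics are deidentified, as Ethical Considerations requires removal of identifiers before analysis.
2. Report KB-sourced listings and reviews as implementation delivery.
3. Use only organization- or user-originated listings as the community indicator, expressed as a monthly rate in both the intervention and comparison periods.
4. Exclude KB-authored reviews and comments from the community-level effectiveness metrics.
5. Relabel the total count in Variables and Outcomes – Implementation as growth in listings. The modified Mobile App Rating Scale cannot replace it as an awareness measure, because it belongs to the pilot, which ends before deployment.
6. For the other engagement metrics, a sensitivity analysis without KB, staff and pilot accounts is enough. Removing pilot participants from the main series is debatable, since they are intended users.

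The cost is a small tagging and linkage step before deidentification, some rewording, and lower counts for the community indicators. The Results section says that the interrupted time series and data analysis had not begun at submission, so the change can be made before any result is seen.
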